### *The Climate Schools program:*

The Climate Schools program aims to reduce the use of Australia's most commonly used licit and illicit drugs: alcohol and cannabis, and related harms. The program was pioneered by CI [name], CI [name] and AI [name] and is based on the effective harm-minimisation approach to prevention ([name] et al., 2009a; 2009b; 2009c; McBride et al., 2006; Vogl et al., 2009). The Climate Schools program consists of twelve 40-minute lessons and is designed to fit within the school health curriculum. It is facilitated by the internet which guarantees complete and consistent delivery whilst ensuring high implementation fidelity. It uses cartoon storylines to engage and maintain student interest and involvement over time (Schinke et al., 2004). The first six lessons focus specifically on alcohol and are delivered approximately six month prior to the remaining six lessons which focus on cannabis. The first part of each lesson is completed individually over the internet where students are engaged through cartoon storylines which impart information about the short- and long-term effects of alcohol and cannabis, normative alcohol and cannabis use, refusal skills, and first aid. Students are provided with confidential login details to access the Climate website. The second part of each lesson is a group or class activity delivered by the teacher which reinforces the information in the cartoons and allows interactive communication between students. Teachers are provided with a manual containing the activities, implementation guidelines, links to the education syllabus and summaries for each lesson. (To view the Climate Schools program, visit [www.climateschools.com](http://www.climateschools.com) and logon using the Username: 'Teacher' and Password: 'London').

### *The Preventure program:*

The Preventure program is a brief personality-targeted substance use preventive intervention for high-risk adolescents aged 14-15 years. Unlike universal programs, this selected personality-targeted approach addresses four personality risk-factors for early-onset substance misuse and other risky behaviours: Sensation Seeking, Impulsivity, Anxiety Sensitivity and Hoplessness (Woicik et al., 2009). The Preventure program is also consistent with new models which conceptualise substance use as being driven by personality traits such as impulsivity and disinhibition (Dick et al., 2008). This program involves two 90-minute group sessions which are carried out by a trained facilitator and co-facilitator. In the first session, participants are guided in a goal setting exercise, designed to enhance motivation to change behaviour. Psycho-educational strategies are used to teach participants about their target personality variable and associated problematic coping behaviours like

avoidance, interpersonal dependence, aggression, risky behaviours and substance misuse. They are then introduced to the cognitive behavioural model and guided in breaking down personal experience according to the physical, cognitive and behavioural components of an emotional response. A novel component to this intervention approach is the fact that all exercises discuss thoughts, emotions and behaviours in a personality-specific way, e.g. identifying situational triggers and cognitive distortions related to Sensation Seeking specifically. In the second session, participants are encouraged to identify and challenge personality-specific cognitive distortions that lead to problematic behaviours. Preventure is the first and only targeted school-based alcohol and illicit drug prevention programme that has been shown to prevent growth in alcohol and substance misuse in Canada and the UK ([name] et al., 2006; 2008; 2010).

*The CAP Intervention:*

The CAP intervention will combine the Climate Schools and Preventure programs with the aim of providing a comprehensive ‘universal’ and ‘targeted’ model to prevent substance use and related harms in Australian adolescents. The CAP study has a logo that will be used on all study materials (see Figure 1).

***Medication(s)/treatment(s) permitted (including rescue medication) and not permitted before and/or during the trial***

N/A

***Procedures for monitoring subject compliance***

Participants in the Climate Schools condition will be required to attend sessions as they will be implemented as part of the PDHPE school classes. Those in the Preventure condition will be sent reminder emails for the two focus groups. The number of sessions attended will be recorded for each participant.

## Assessment of Efficacy

### *Specification of the efficacy parameters*

Treatment efficacy will be determined by analysing changes in three outcome measures over the study period:

1. The uptake and harmful use of alcohol and illicit substances
2. Substance use related harms
3. Mental health comorbidity

This information will be gleaned from the baseline and follow-up assessments using reliable and well-validated measures.

The assessment surveys include the following measures:

1. *Demographic data* including gender, age, academic performance, and truancy rates will be obtained to determine baseline equivalence of the groups
2. *The Substance Use Risk Profile Scale (SURPS)* will be used to assess for variation in personality risk for substance abuse/dependence along 4 dimensions: Sensation Seeking, Impulsivity, Anxiety Sensitivity and Hopelessness. Students who score more than one SD above the school mean on any of the four personality risk subscales will be categorized into these sub-groups and will be invited to participate in the Prevention intervention if they are randomised into the CAP or Preventure groups. If a student has high scores on more than one subscale, they will be assigned to the group in which they showed the most statistical deviance according to z-scores;
3. *Alcohol and cannabis knowledge, Patterns of Alcohol use, Cannabis use and Other substance use, and Attitudes about alcohol* will be assessed using questionnaires adapted from the School Health and Alcohol Harm Reduction Project (SHAHRP; McBride et al., 2003; 2006) and also based on the questions from the National Drug Strategy Household Survey 2007;
4. *Harms caused by cannabis use* will be measured using 12 items from the SHAHRP survey instrument and a set of questions adapted from the Adolescent Cannabis Problems Questionnaire (Martin et al., 2006);
5. Five questions will be used to assess student's *intention to use alcohol and illicit drugs* in the 'future'
6. *The Resistive Self-Regulatory Efficacy Scale* will be used to measure participants' perceived efficacy to resist peer pressure to engage in high risk activities (Bandura et al., 2003);
7. The *Kessler 6 scale* (Kessler et al., 2002) will be used to assess past-month psychological distress
8. The *Strengths and Difficulties Questionnaire* (Goodman, 1998) will be used to assess both positive and negative attributes of the students;
9. *Depression and Anxiety symptoms* will be measured using the depression and anxiety subscales from the Brief Symptom Inventory (BSI; Derogatis 1993);
10. The *Reactive-Proactive Aggression Questionnaire* (Raine et al., 2006) will be used to measure students' levels of reactive and proactive aggression;
11. The *Bullying Questionnaire* comprises questions taken from a large international study entitled Health Behaviour in School-aged Children (HBSC), and are originally

taken from the revised Olweus Bully/Victim Questionnaire (Olweus, 1996), and the Youth Risky Behaviour Survey (Brener et al., 1995);

12. The *Thoughts and Feelings Questionnaire* is a brief questionnaire on psychotic symptoms derived from the Personal Assessment and Crisis Evaluation (PACE, Phillips et al., 2000) and the Prodromal Questionnaire (PQ; Loewy et al., 2005);
13. Symptoms of alcohol abuse will be assessed using the Diagnostic Interview Schedule for Children (DISC-IV; Shaffer et al., 2000).

***Methods and timing for assessing, recording, and analysing of efficacy parameters***

Assessment surveys will be administered at baseline, and at 6, 12, 18, 24, 30, and 36 months post-baseline. Participating schools have the option of completing these assessments online or by paper-and-pencil. Data will be collated and analysed at each assessment stage using PASW Statistics 18. Hierarchical Linear Modelling (HLM) will be used for clustered data.

**Assessment of Safety*****Specification of safety parameters***

It is possible that the Preventure sessions may uncover psychological distress in some participants. These sessions will be run by registered Psychologists who are trained to manage individuals with current psychological distress. These Psychologists will undergo specific training for implementing Preventure and this will involve how to deal with situations where students become distressed.

***The methods and timing for assessing, recording, and analysing safety parameters***

The Psychologists running the Preventure sessions will be trained to identify and deal with situations in which participants become distressed.

***Procedures for eliciting reports of and for recording and reporting adverse event and intercurrent illnesses***

Situations in which participants in the Preventure sessions become distressed will be recorded in the Psychologists session notes. The Psychologists will also be required to report these incidents to the project co-ordinator and will then decide if any further action is necessary and whether the appropriate school staff member will need to be notified (with the consent of the student).

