Alcohol and other drug use is common in Australia and the burden of disease, social costs, and disability associated with this use is considerable (1, 9, 10). The peak of this disability occurs in those aged 15-24 years and corresponds with the typical age of initiation of alcohol and drug use (11). The high prevalence of substance use amongst adolescents is of particular concern given that early initiation to drug use is a risk factor for the development of substance use disorders, comorbid mental health problems, juvenile offending, impaired educational performance and early school dropout, all of which negatively impact on both current functioning and future life options (12-15).

To reduce the occurrence and cost of such problems, prevention is essential and needs to be initiated early before harmful patterns of drug use are established and begin to cause disability (16, 17). Although an array of school-based prevention programs exist (18-23), the majority show minimal effects in reducing drug use and related harms (24-27), and some have even reported iatrogenic effects (28). The most common factors which impede on effectiveness are; the focus on abstinence-based outcomes (29, 30), and implementation failure (31-33).

There are two common approaches to school-based drug education; 'universal' and 'targeted' (34). The targeted approach involves delivering programs which target specific populations, such as individuals at greatest risk for developing substance use problems. On the other hand, the universal approach aims to deliver interventions to all students regardless of their level of risk for drug use, and focus largely on teaching drug resistance skills (35). The major advantage of this approach is that it has the ability to reduce substance use on a larger scale (36, 37). Regardless of the approach, programs which have demonstrated the most success in increasing drug related knowledge, decreasing pro-drug attitudes and decreasing drug use behavior, are those programs which have a harm-minimization goal, are implemented correctly and use interactive delivery techniques (20, 38-40).

Given that schoolbased drug prevention is the primary means by which drug education is delivered, it is essential to focus on increasing program efficacy. Ideally, preventive interventions should aim to delay onset in both adolescents with low-risk profiles who may

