### ***Summary of the known and potential risks and benefits, if any, to human subjects***

Based on prior evidence for the efficacy of the Climate Schools and *Preventure* programs (Castellanos & [name], 2006; [name] et al., 2008; 2010; [name] et al., 2009a; 2009b), it is possible that students randomized to these groups will benefit from these programs. These programs have been shown to reduce along with associated harms including mental health co-morbidity.

At the start of each baseline and follow-up survey session the facilitator will make it clear to the students that their confidentiality will be strictly maintained. Students will also be made aware of their options if any of the issues raised in the survey has made them feel uncomfortable, sad or worried. The following will be explained to them (in addition to being included at the end of each questionnaire): 'If any of the issues raised in this survey have made you feel uncomfortable, sad or worried, there are people you can reach out to. These could be your friends, family or teachers. You can also phone Kids Helpline on [name] for free, confidential help with any issues you want to talk about'.

It is possible that the *Preventure* sessions may uncover psychological distress in some participants. Systems will be in place to deal with such psychological distress. The *Preventure* sessions will be run by registered Psychologists who are trained to manage with individuals with current psychological distress. These Psychologists will also undergo specific training for implementing *Preventure* from CI [name], and this will involve how to deal with situations when students become distressed. Students will be reminded that they have the option of withdrawing from the study at any time without having an effect on their relationship with the school or the University of NSW. If they choose to withdraw due to psychological distress, the appropriate school staff member will be notified (with the consent of the student/parent?) and the necessary systems will be put in place.

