***Criteria for the termination of the trial***

There are no criteria for the termination of the trial. There have been no significant adverse events in prior research to indicate termination is necessary.

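### Adverse events are elicited and recorded only in Preventure sessions; survey distress, named as a risk for every student, has no recording route, and the symptom scales surveyed in all arms are not designated as harm outcomes

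*Protocol*

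**What the plan says.** The Protocol's Assessment of Safety chapter is about Preventure throughout.

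- **Safety parameter:** "It is possible that the Preventure sessions may uncover psychological distress in some participants". No other parameter is given.
- **Method, timing and analysis:** "The Psychologists running the Preventure sessions will be trained to identify and deal with situations in which participants become distressed". No timing or analysis is stated.
- **Recording:** "Situations in which participants in the Preventure sessions become distressed will be recorded in the Psychologists session notes".
- **Reporting:** "The Psychologists will also be required to report these incidents to the project co-ordinator".
- **Follow-up after an event:** also written for students who find the Preventure sessions distressing.

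Other parts of the Protocol bear on the same question.

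- The summary of risks and benefits foresees distress from the surveys, which every student in every arm completes. It has facilitators read out a message beginning "If any of the issues raised in this survey have made you feel uncomfortable, sad or worried", followed by sources of support. No record of such distress is called for.
- Specification of the efficacy parameters lists scales given to all participants: the Kessler 6 (K6) for past-month distress, the depression and anxiety subscales of the Brief Symptom Inventory (BSI), the Strengths and Difficulties Questionnaire (SDQ), and an instrument that "is a brief questionnaire on psychotic symptoms". All stand under efficacy, and the trial hypotheses speak only of reductions.
- Direct Access to Source Data/Documents has the investigators and staff review whatever adverse event reports come in, but sets up no further source of reports.
- Criteria for the termination of the trial rests on earlier research: "There have been no significant adverse events in prior research to indicate termination is necessary".

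**The concern.** Who records events, where and when is a data-collection rule. If it differs between arms, no later analysis plan can recover what was not recorded. Here the rule follows one program in two of the four arms. Nobody is asked to record an event in a Control school, in a Climate lesson, at a survey session, or in a low-risk student anywhere.

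Three things are at stake. First, a zero in the Control or Climate-only arm would carry no information, so a later statement that no adverse events occurred there could not be supported. Second, the high-risk students in those two arms, who are the natural comparators for Preventure, have no matching record. Third, the data that could support a like-for-like harm comparison are collected but assigned to efficacy. The main models described under Statistics compare average change or counts, and an average can hide a minority who deteriorate while others improve.

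**Working it through.** The plan states no safety figure to reproduce. The check is one of coverage, using the Protocol's own enrolment inputs.

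**Inputs**
- Four arms of 6 schools; Preventure is delivered in two of them (Trial Design).
- 80 students per school, of whom 40% are expected to be high-risk; 24 schools; 1,920 students (The number of subjects planned to be enrolled).
- Only students above the cut-off on the personality risk scale in the Preventure and CAP arms are invited (Specification of the efficacy parameters).

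**Enrolment figures reproduced**
- 24 x 80 = 1,920, as stated.
- 0.40 x 80 = 32 high-risk per school, as stated.

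**Coverage of the written route**
- Reached: 2 x 6 x 32 = 384, and 384 / 1,920 = 20%. This is the number invited, so it is an upper limit on the number attending.
- Not reached: 1,920 - 384 = 1,536 (80%), made up of 2 x 6 x 80 = 960 in Control and Climate-only and 2 x 6 x (80 - 32) = 576 low-risk students in the other two arms.
- High-risk students in all: 24 x 32 = 768. Half of them (384) are in arms with no route.
- Time covered by session notes: 2 x 90 min = 3 hours per invited student. Climate runs 12 x 40 min = 8 hours for 960 students, with no event route.

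**Timing of a usable comparison.** Table 1 puts Preventure in April to September 2012 and the 6-month survey in September 2012. The two overlap, and the K6 looks back one month. The first survey after delivery has ended in all schools is the 12-month wave, February to March 2013.

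**Could the existing scales support a harm comparison?** This is an illustration only. It assumes 10% worsening without the program, a school intraclass correlation (ICC) of 0 to 0.02, two-sided alpha 0.05, 80% power (sum of normal quantiles 2.80) and no dropout.
- *Preventure versus none, high-risk students, 384 per side.* At ICC 0.02 the design effect is 1 + 31 x 0.02 = 1.62, and 384 / 1.62 = 237. For 19% versus 10%, SE = sqrt((0.090 + 0.154) / 237) = 0.032, and 2.80 x 0.032 = 0.090, which equals the difference. At ICC 0 (n = 384) the detectable rate is about 17%.
- *Climate versus none, all students, 960 per side.* At ICC 0.02 the design effect is 1 + 79 x 0.02 = 2.58, and 960 / 2.58 = 372. For 17% versus 10%, SE = sqrt((0.090 + 0.141) / 372) = 0.025, and 2.80 x 0.025 = 0.070, which equals the difference. At ICC 0 (n = 960) the detectable rate is about 14%.

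These figures ignore the limited degrees of freedom from 12 schools per side. They show only that the data already collected are not useless for this purpose.

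**The case against.** The strongest reply is that session notes are an incident procedure, not a comparative endpoint. They are kept where the group session takes place, the incident goes to the co-ordinator, and action is decided. The Protocol plans no comparison of event counts between arms, so nothing it plans is biased by unequal recording. Distress is measured in every arm by the K6, BSI and SDQ, the tests are not stated to be one-sided, and odds ratios are foreseen, so an arm that worsened on average would be seen. Reports from other arms are not excluded, because the investigators review any that arise. A threshold for worsening and a safety table could properly be left to a statistical analysis plan that is not shown.

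Much of this stands, and it rules out three stronger readings that a reader might infer.

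- *That a second named risk, iatrogenic harm, is never captured.* The remark about other school programs, "and some have even reported iatrogenic effects", is background. The Protocol's own risk section does not list it for this trial, and the outcomes that would show it are surveyed in all arms.
- *That distress goes unmeasured outside Preventure.* It is measured by the symptom scales. What is missing is event-level recording and any statement that the scales will be read as harms.
- *That Preventure will look worse than Control by design.* No such comparison is planned. The documents support only that, if one were made, it could not be interpreted.

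The reply does not remove the recording rule itself. Reviewing reports that arise does not create a source for them, and an analysis plan cannot supply events that nobody was asked to write down.

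**Conclusion.** The point holds in a limited form. As written, adverse events are elicited and recorded only as distress in Preventure sessions, for about 384 of 1,920 planned students in two of four arms. Survey distress, foreseen for every student, has no recording route. Event counts therefore cannot be compared between arms or reveal harm in the Control and Climate-only arms. The scales that could serve that purpose are designated for efficacy alone.

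The 384 rests on the Protocol's expected 40% high-risk share and on every invited student attending. The detectable differences rest on an assumed ICC and worsening rate, and the verdict does not depend on them.

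**What to change.** Amend the Assessment of Safety chapter in three places.

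1. **Same recording in all arms.** The Research Officers who run the assessments are already present and are blinded to allocation. Have them log any distress at a survey session on one short form, identical in all four arms and at every wave, and report the counts by arm.
2. **Designate harm outcomes.** Name the K6, BSI and psychotic-symptom scores as harm outcomes as well as efficacy outcomes. Report by arm the proportion worsening from baseline by a pre-set amount, two-sided and with school clustering, in all students for Climate and in high-risk students for Preventure. Place the main harm comparison at 12 months, the first wave after delivery has ended in all schools, because the September 2012 survey overlaps Preventure delivery.
3. **Label the session notes.** State that counts from Preventure session notes are descriptive and are not compared between arms.

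The cost is a one-line form at survey sessions and one extra table per wave, with the possibility of a result less favourable to the programs. One limit remains: a scale read at 12 months will not show brief distress soon after a session or lesson. The extension application in the same document reports the surveys up to 3 years as complete. For those waves only the second and third changes can still be made, from data already held.

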***The type and duration of the follow-up of subjects after adverse events***

If students find the Preventure sessions too distressing they will be reminded that they have the option of withdrawing from the study at any time. If the Psychologists and project manager deem it necessary (and with the consent of the student) an appropriate school staff member will be notified. The student will then be in the care of the staff member and will be dealt with according to school policy.

